### Description of the intervention

The intervention will be performed by the regular health professionals who usually treat the patient (psychiatry and mental health nursing), after receiving specific training and after the intervention have been validated by specialists from the Addiction Network and the Pneumology Service at the Reina Sofía Hospital in Córdoba, Spain.

#### Control group

The control intervention lasts 30 min and will be structured around the 5 A’s technique (Ask, Advice, Assess, Assist and Arrange) [27]. Data will be collected on the patient’s smoking record, level of consumption and their individual level of motivation. Their smoking habit, personal circumstances and the general health risks derived from their current consumption will be discussed with the patient following the recommendations of the Treating Tobacco Guideline [33] and on the basis of the Motivational Interviewing [34]. The risks and benefits will be weighed and the patient’s perceived self-efficacy will be assessed in order to generate greater motivation. Depending on the degree of motivation, the idea of setting a deadline for the change in habit, specific treatment and regular follow-up will be put forward. In order to reinforce the message, informative materials stressing the general health benefits of quitting smoking will be provided, and patients will be given a direct contact number to request an urgent appointment for support and specific treatment, as needed.

#### Experimental group

This group will go through a spirometry study for a lung age and obstruction degree determination. The anti-smoking intervention will follow the same duration and general structure of the control group. In this case, when talking about the health risks, personalized information about the lung damage and prevention opportunities will be included. It will teach the patients about comparing lung age with chronological age and explain how the formula is calculated and the origin of the damage. After evaluating their COPD, the patients will be informed about its existence and staging. Depending on the damage found, the generation of motivation will focus on different prevention methods. Likewise, after the motivation level is set, the patients will be offered the option of treatment and regular follow-up. The intervention will be strengthened by motivational messages (designed by specialists from our Addiction Network) in an attempt to give continuity to personal message based on MI—half of which are linked to the possibility of preventing respiratory damage—and sent to the patient's mobile phone via SMS during the 3 months after the face-to-face intervention, with a decreasing rate: three messages per week in the first month, and two and one per week in the following months, respectively (see Table 1 for examples of these messages) [35]. Patients without mobile phones will receive a call on their phone to convey the same messages.

**Table 1 Tab1:** Examples of text messages (SMS) sent to patients in the intervention group

Wanting to smoke is temporary, but the damage to your lungs is permanent – Which kind of suffering do you want to choose?	
The pleasure of breathing in deeply and enjoying a beautiful spring morning would be easier with cleaner lungs. How about trying it?	
Did that little run down the street leave you breathless? Ever thought about giving up smoking? Life is much more bearable with clean lungs.	
If your lungs could speak, they’d be really angry at how you are treating them. It’s up to you – you can make your life better.	
Better health and lung capacity, more cash to spend and less smelly clothes. That’s what you gain when you give up smoking. Difficult to imagine giving up? You’re not alone! Come and see us and we’ll plan it together.	

### Safety protocol

The anti-tobacco intervention can only be given to clinically stabilized patients. In these cases, their psychiatrist will confirm whether they can be classified as psychopathologically stable prior to the intervention scheduled for the second visitInformation about individual lung damage will be offered based on the prevention opportunities and following the general MI model, as in the rest of the protocol. To guarantee it, the messages will be generated based on respiratory variables and by the team of researchers— psychiatrist, expert physicians on addiction and pneumologist specialists—and sent on the Redcap platform to the center researcherWhen they are first informed about the intervention and prior to the start of the intensive mobile phone intervention with SMS, the patients are asked once again if they wish to continue with the study. In each message sent, a phone number is included where the patient can request not to receive any more messages if they so wishThe patient is given the opportunity to contact the specialized addiction service network, made up of physicians who routinely treat patients with SMI who are trying to quit smoking and do not receive treatment due to their possible lack of psychopathological stabilityThe researcher will make a written record of any COPD diagnosis performed, which, in mild cases, is sent to the primary care physician and in moderate or severe cases, to the pneumology service

### Patient and public involvement

All the patients will receive enough information about the study by a resume paper with the principal objectives and methodology of the research. As was explained in Fig. 1, only the patients that give their agreement to participate will be included in the study. If the patients want, they will give us their contact details to receive the principal results published in the future.

### Result variables

Lung damage variables2.1Main variable:Presence of COPD (FEV1/forced vital capacity (FVC) < 0.7, confirmed after bronchodilation) and staging (FEV1 > 80% – mild, FEV1 50–80% – moderate, FEV1 30–49% – severe)2.2Secondary variable:Percentage of FEV1 compared with expected level. Calculation of lung age based on the Fletcher and Peto [36] modelEfficiency variables2.1Main variable:Smoking cessation, defined as self-reported abstinence over the previous 7 days, confirmed by *cooximetry* with expired carbon monoxide (CO) < 10 particles per million (ppm)2.2Secondary variables:Increased levels of motivationNumber of attempts to quit and total duration in days of abstinence, as reported by the patientSmoking cessation objectified by cooximetry (< 10 ppm) at scheduled follow-up appointmentsReduction in the number of cigarettes/day (CPD) smoked, as reported by the patient and confirmed by expired CO after 3, 6 and 12 months

### Data collection and monitoring (see Fig. 2)

Sociodemographic data:Age, gender, educational level, marital status, number of children, employment status, place of residence, home environment (including other members of the household who smoke) and incomeClinical variables:Confirmation of diagnosis. Schizophrenia and BD sections of the Spanish version of the Structured Clinical Interview for DSM-IV Axis I Disorders (SCID-I) [37]Psychiatric disease variables, as reported by the patient and confirmed by their clinical history. Age of onset, illness duration, number of suicide attempts and number of hospital admissions in the last 5 yearsClinical stability will be assessed by the reference psychiatrist at each center and evaluated by the HDRS [38] and YMRS [39] scales for BD and PANSS [40] for schizophreniaAnxiety symptoms of anxiety. Hamilton Anxiety Rating Scale (HARS) [41]Global functioning. Global Activity Assessment Scale (GAAS) [42]Psychopharmacological treatment at study entry and during the studyComorbidity (from medical history). Anthropometric measurements and vital signs (by nurse, following the schedule):Hypertension, diabetes, dyslipidemia, peripheral vascular disease, heart disease and oncological diseaseHeight, weight, Body Mass Index (BMI), abdominal perimeter, oxygen saturation, blood pressure and heart rateSmoking habitHistory of consumption: age of onset, years of consumption and accumulated consumption (number of packs/year)Current consumption and dependency level:Type and brand of tobacco and CPDExpired CO, reported as ppm, measured with an MD Diagnostic CO Check+ cooximeter (concentration range 0–99 ppm, sensitivity 0.1 ppm). The measurements will be obtained between 11.00 a.m. and 01.00 p.m., with a cut-off point for active smokers of 10 ppm, as in previous references [43].Dependence on nicotine, as evaluated by the Fagerström Test for Nicotine Dependence (FTND) [44]: mild (0–3), moderate (4–7) and severe (8–10)History of previous attempts to quit smoking (minimum 24 h trying to quit):Record of the number of attempts lasting more or less than 1 month. Total sum of days of abstinence reportedPrevious specific treatments, adverse reactions or psychopathological decompensationMotivation to quit smoking:Richmond Test [45]: low (0–4), moderate (5–6) and high (7–10)Analogue visual scale from 1 to 10, measuring the patient’s desire to quit smoking and perceived self-capacity [46]Prochaska and DiClemente’s Stages of Change (SOC) [47]Request for referral to specific treatment of Addictions Network:Number of appointmentsTreatment offeredUse of other substancesThe consumption of other substances—such as alcohol, cannabis, cocaine, stimulants, hallucinogens, heroin, methadone, other opiates or inhalants—will be measured using the “Drug Use Table: Individual Substances” section of the Spanish Addiction Severity Index, 6th version (ASI6) [48]We will record the age of the first consumption, years of regular consumption, consumption for 50 or more days in the patient’s life and consumption over the last 30 days. Consumption will also be calculated for caffeine, measured as cups of coffee/day (one cup of coffee = one energy drink = two cups of tea = three cups of soft drinks [49]), and for cannabis, measured as type (resin or leaf), consumption method (joint or vapor inhalation) and number of joints/year (52 weeks × number of joints/week/365 × number of years smoking) [50]. Patients with cocaine or heroin habits will be noted if the substance is inhaledPhysical activityThe amount of physical activity will be calculated through the self-administered International Physical Activity Questionnaire (IPAQ), used in its shortened version [51] and validated in Spanish [52]. The unit to measure energy expenditure is the MET (Metabolic Equivalent of Task), and the total expenditure in METs-minute/week is calculatedNeuropsychological evaluationIn order to evaluate neurocognitive functioning and any possible changes after the intervention, the Digit Span Test will be used in reverse order or backwards (WAIS-III) [53], together with parts A and B of the Trail Making Test [54], which measure verbal working memory, processing speed and executive attention, respectively

**Fig. 2 Fig2:**
[figure not shown]
Scheduled tasks

### Spirometry

To validate the equipment used and check its characteristics, the test and criteria for quality control will be used for acceptability and repeatability of the results; the standardization criteria set down by the American Thoracic Society and the European Respiratory Society (ATS/ERS) [55] will be followed (see Table 2).

**Table 2 Tab2:** Protocol for evaluation and diagnosis of respiratory pathology

Evaluation and validation	Persons responsible and venue	Nursing team (Mental Health Unit)
	Training	Accredited training^a^ given by the pulmonology service of Reina Sofía Hospital, Córdoba, Spain
	Skills acquired	Calibration, preparing patients, performing maneuvers, bronchodilation and repetition of spirometry
	Automatic Validation	Automatic validation Maximum of 8 maneuvers before achieving a minimum of 3 maneuvers of an acceptable standard^b^ Classification and automatic choice of the 2 best curves with repeatability criteria^c^
	Reversibility test	Repetition of 3 acceptable maneuvers 15 min after inhalation by bronchodilator (salbutamol, 400 μg)
Quantification and diagnosis	External Validation	External validation curves and volumes are assessed by a single researcher, head of the functional test unit of the Pneumology Service at the Reina Sofía Hospital, Córdoba, Spain
	Volumes	Forced vital capacity (FVC), forced expiratory volume (FEV1) and the quotient of the two (FEV1/FVC)
	Calculation of lung age	Automatic and externally verified
	Diagnosis and staging	Presence and degree of respiratory obstruction, according to criteria established by the Global Initiative for Chronic Obstructive Lung Disease (GOLD) guideline

^a^The accredited training consisted of learning the theoretical principles behind the test, how to handle and look after the material and how to perform spirometry maneuvers and secure the selected measurements

^b^Acceptability criteria: the flow/volume curve must not contain artifacts, must start well and should last for at least 6 s

^c^Repeatability criteria: the two highest FVC and the two highest FEV1, with a difference between them of less than 0.15 L

### Respiratory variables

Respiratory symptoms and impact on quality of life [56]Severity of dyspnea, using the Modified British Medical Research Council (mMRC) scale [57]

### Statistical analysis

The statistical analysis will include all the patients randomized to both branches according to an intention-to-treat approach. The main variable for smoking cessation will be analyzed using the chi-square test for qualitative variables, which in this case consist of the differences between the control and intervention groups. The effect size will be expressed as relative risk (RR), absolute risk reduction (ARR) and the number needed to treat (NNT), with the corresponding 95% confidence interval (CI). The secondary variables will require the comparison of the average values of the quantitative variables between groups (level of motivation, consumption of tobacco according to CPD and expired CO) and will be carried out using Student’s *T* test and its respective post-hoc correction tests. The Mann-Whitney *U* test will be used for the non-parametric equivalent. The association between the quantitative variables will be evaluated using bivariate correlation tests, such as Pearson’s linear correlation coefficients (parametric test) or Spearman’s correlation coefficients (non-parametric test). The respiratory variables for the presence of COPD and its staging will require a descriptive analysis and the results will be presented as frequencies and percentages. Logistic regression models will be used for the multivariate analysis. To control any effects in the comparison between groups caused by contact with the addiction treatment network or the neurocognitive evaluation, the variables associated with these events will be collected and the corresponding adjustments made in the analysis.

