## Methods/design

### Study design

This is a multicenter, open, randomized and prospective study, with a 12-month follow-up period. Nine Mental Health Centers from the South of Spain, serving both rural and urban populations in the provinces of Córdoba, Jaén, Málaga and Granada, will take part in the study.

The study protocol (version 1: 11/2016) has been approved by the Ethics Committee of Reina Sofía Hospital in Córdoba, Spain, and informed consent will be obtained from each participating patient before recruitment. The http://ClinicalTrials.gov identifier was NCT03583203.

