**Fig. 1 Fig1:**
[figure not shown]
Flow diagram of study design

Recruitment of at least 204 patients who meet all the inclusion criteria and none of exclusion criteria will be carried out over 1 year and follow-up appointments will be arranged after that.

Inclusion criteria: (1) patients aged between 40 and 70 years; (2) confirmed diagnosis of BD or Schizophrenia according to *Diagnostic and Statistical Manual of Mental Disorders, 4th edition, text revision* (DSM-IV-TR); (3) active smokers who currently consume at least 10 CPD, with a cumulative consumption of 10 packets/year or more; (4) have signed an informed consent to participate in the study.

Exclusion criteria: (1) previous respiratory diagnosis of: asthma, cystic fibrosis, tuberculosis, simple chronic bronchitis, restrictive pulmonary disease or bronchiectasis; (2) acute respiratory symptoms; (3) heart disease or advanced oncological processes; (4) existence of a pathology which makes it advisable not to perform spirometry (recent pneumothorax, recent thoracic or abdominal surgery, aortic aneurysm, unstable angulation, retinal detachment, facial hemiparesis or oral/dental problems); (5) patients who, due to their intellectual disability or mental pathology, do not understand or cannot be forced to perform spirometry; (6) clinical instability with results of over 14 points on the Hamilton Depression Rating Scale (HDRS), a Young Mania Rating Scale (YMRS) score of over 6 or a Positive and Negative Syndrome Scale (PANSS) score of over 70.

The randomization will be carried out using the *Redcap* [32] program, as implemented by the Bioinformatics Unit of IMIBIC (the Maimónides Institute of Biomedical Research in Córdoba, Spain). It will be centralized, performed in permuted blocks and stratified by center, age, gender and pathology. The ratio will be 1:1 for each arm. The research staff will have no knowledge of the assignment until the patient signs their informed consent and has been included in the system (which will automatically assign the patient, once included, to a particular arm).

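### Randomisation is stratified by four factors, but the primary chi-square and its RR, ARR and NNT use none of them; the cost is small and an 8-cell Mantel-Haenszel analysis would align the two

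*Protocol article*

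**What the plan says.** Under Recruitment and randomization, the Protocol article describes allocation thus: "It will be centralized, performed in permuted blocks and stratified by center, age, gender and pathology". It adds that "The ratio will be 1:1 for each arm". Study design names the sites: "Nine Mental Health Centers from the South of Spain". The inclusion criteria require a "confirmed diagnosis of BD or Schizophrenia", so pathology has two levels, and admit "patients aged between 40 and 70 years". The article gives no age cut-points and no block size, which is ordinary condensation and is not criticised here.

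Under Statistical analysis, the primary endpoint is handled in one sentence: "The main variable for smoking cessation will be analyzed using the chi-square test for qualitative variables". The contrast is control against intervention, and the effect is reported as RR, ARR and NNT with 95% confidence intervals. No stratification factor is mentioned. The section also says that "Logistic regression models will be used for the multivariate analysis", without listing covariates. The only adjustments it names are for contact with the addiction network and for the neurocognitive evaluation.

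**The concern.** Stratified blocks force the arms to be more alike on the stratification factors than chance alone would make them. If those factors predict quitting, the true sampling variance of the difference is smaller than the variance the crude chi-square assumes. The test then rejects too rarely under the null, and the crude intervals for the risk difference (hence NNT) and RR are somewhat too wide. The usual answer is to carry the main stratification factors into the primary analysis.

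The number of cells adds a second reason. With few patients per cell many blocks stay incomplete, so some imbalance on the chosen factors can remain, and an analysis stratified by those factors would account for it.

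With few quitters expected, the choice of strata also affects power. It is better fixed in advance than after the data are seen.

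**Working it through.** **Inputs.** From the article: 9 centres; 2 diagnoses; 204 patients, 1:1; 12-month abstinence of 3% and 15%; 95% confidence; 80% power; 85 per arm plus 20%. Two levels are taken for gender. Assumed because the article gives no figure: two age bands (three as a check), blocks of 4 (2 and 6 as checks), and the prognostic strength of the factors.

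**The plan's own figure.** Two-proportion formula with unpooled variance, two-sided 5%: n = (1.96 + 0.8416)² × (0.03 × 0.97 + 0.15 × 0.85) / 0.12² = 7.849 × 0.1566 / 0.0144 = 85.4. This agrees with 85 (86 if rounded up), and 2 × 85 × 1.2 = 204.

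**Events.** 102 × 0.03 + 102 × 0.15 = 3.06 + 15.30 = 18.4 quitters, about 3 of them controls.

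**Cells.** 9 × 2 × 2 × 2 = 72, and 204 / 72 = 2.8 patients per cell. With three age bands there are 108 cells and 1.9 per cell. Any stratification by age needs at least two bands, so 72 is a minimum.

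**Balance** (1,000 simulated allocations each, equal expected cell sizes, two age bands). Difference in arm totals:

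| Allocation | Mean | 95th percentile |
|---|---|---|
| Simple randomisation | 11.0 | 28 |
| Stratified, blocks of 2 | 4.8 | 12 |
| Stratified, blocks of 4 | 6.4 | 16 |
| Stratified, blocks of 6 | 7.8 | 18 |

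With blocks of 4, about 49 of the 72 cells hold fewer patients than one block and about 18 contain one arm only. A difference of 16 means 94 against 110. Within one diagnosis the 95th percentile is 11, against 19 under simple randomisation. The mean difference in arm totals falls by 1 − 7.8/11.0 = 29% (blocks of 6) to 1 − 4.8/11.0 = 56% (blocks of 2).

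**Type I error and power** (6,000 simulated trials per setting, blocks of 4, no losses, no continuity correction). The null is 9% in both arms; the alternative is 3% against 15%. OR is the assumed prognostic odds ratio for each of age, gender and diagnosis, with a matching centre effect. CMH is the Cochran-Mantel-Haenszel test.

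| OR | Quantity | Chi-square | CMH, 8 cells | CMH, 72 cells |
|---|---|---|---|---|
| 1 | Type I | 5.0% | 4.9% | 5.1% |
| 1 | Power | 89.1% | 88.6% | 82.5% |
| 2 | Type I | 4.3% | 4.3% | 4.7% |
| 2 | Power | 88.9% | 89.1% | 83.4% |
| 3 | Type I | 4.7% | 5.1% | 4.9% |
| 3 | Power | 88.5% | 89.4% | 84.9% |

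The simulation standard error of a 5% rate is √(0.05 × 0.95 / 6000) = 0.28 points. With OR 3 but unstratified allocation, the crude test rejected in 5.5% of null trials. That fits the explanation that the stratification is what makes the crude test conservative.

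Further runs of the same design with strong factors (for instance log-odds of 1.4 for diagnosis and 0.7 for age and gender, centre SD 0.5) gave type I error of 3.7% and 4.1% for the chi-square, against 4.2% and 4.6% for the 8-cell test. Power was 88.6-89.3% against 89.2-89.9%. With effects about halved, power was 88.5% against 88.1%. With none, it was 88.9% against 88.4% in one run and 89.2% against 88.5% in another.

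**The case against.** The strongest defence is that the crude chi-square is valid. Any shortfall in its type I error is on the conservative side, and the 8-cell test does no better in some settings: both give 4.3% at OR 2. The power difference changes sign. The 8-cell test gains 0.6 to 0.9 points with strong factors and loses about 0.5 to 0.7 points with none. The article says nothing about prognostic strength. The 8-cell analysis is itself sparse: with 3.06 expected control quitters, about 8 × exp(−3.06/8) = 5.5 of the 8 cells would have none. It also leaves out centre, so it does not use every stratification factor. All of this stands and limits the size of the point. It does not remove the mismatch, because the article positively names a primary test that uses none of its stratification factors.

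Three stronger readings are tempting, and the article does not support them.

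- A reader might infer that 72 cells defeat the stratification. They do not: imbalance stays well below that of simple randomisation. The SD of the difference in arm totals is about 7.9 with blocks of 4, against √204 = 14.3. A one-SD imbalance, about 98 against 106, moves the power of the chi-square only from 89.2% to 88.6%.
- A reader might infer that the planned logistic regression would break down with about 18 events. The article lists no covariates apart from the two named adjustments and does not call that model a fallback for the primary test. An overloaded model would be the reader's own construction, and the models may well include the stratification factors.
- A reader might conclude that the remaining recruitment should be re-stratified. Nothing here requires it.

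**Conclusion.** The point holds as a modest mismatch between design and primary analysis, not as a threat to validity. With strongly prognostic factors the crude test runs at about 4% in some settings instead of 5%, and its intervals are slightly too wide. With weak factors the difference is negligible. The 8-cell analysis gains at most about one point of power and may lose about half a point if the factors do not predict quitting. Stratification over at least 72 cells reduces imbalance but cannot guarantee balance.

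These sizes rest on two age bands, blocks of 4, assumed prognostic effects and complete outcomes for 204 patients. The direction for interval width follows from the variance argument; widths were not simulated separately. The mismatch itself and the 72-cell minimum need only the article's text and two levels for gender.

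**What to change.** State that the primary analysis is a Cochran-Mantel-Haenszel test without continuity correction, over diagnosis x age group x gender (8 cells), using the categories entered at randomisation. Report the Mantel-Haenszel risk difference and RR with 95% confidence intervals, and derive NNT from that risk difference. Keep the plain chi-square with crude RR, ARR and NNT as a sensitivity analysis. Say explicitly that the strata are not crossed with centre, because using all 72 cells would cost about 4 to 7 points of power (82.5-84.9% against 88.5-89.1% for the chi-square).

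The cost is a change of wording in the analysis section, made before outcome data are examined. The factors are already held in the randomisation system. Neither the randomisation nor the data collection needs to change.

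### The t-tests on motivation, cigarettes per day and expired CO leave the baseline value out as a covariate and do not fix the quantity or visit compared; ANCOVA would be more precise at almost no cost

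*Protocol article*

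**What the plan says.** The Statistical analysis section of the protocol article fixes the method for the quantitative secondary outcomes. It is a "comparison of the average values of the quantitative variables between groups (level of motivation, consumption of tobacco according to CPD and expired CO"), done by Student's t "test and its respective post-hoc correction tests", with Mann-Whitney U as the non-parametric counterpart. The only regression named is for binary outcomes: "Logistic regression models will be used for the multivariate analysis". The only adjustments named are for contact with the addiction treatment network and for the neurocognitive evaluation.

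The Result variables section words the same outcomes as changes: an increase in motivation and a reduction in cigarettes per day (CPD). It gives visit times for the CPD outcome, "as reported by the patient and confirmed by expired CO after 3, 6 and 12 months". The readable text gives none for motivation, and the schedule figure is not shown.

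Baseline values exist. Eligibility requires "active smokers who currently consume at least 10 CPD". The control intervention records the patient's "smoking record, level of consumption and their individual level of motivation", and the experimental intervention follows the same general structure. Motivation is scored on the Richmond Test, banded as "low (0–4), moderate (5–6) and high (7–10"), among other scales. Expired CO is listed with current consumption under Data collection and monitoring.

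**The concern.** A two-sample t or Mann-Whitney test has no covariate and no time term. The baseline value of a smoking or motivation measure usually predicts its later value, so leaving it out of the model leaves explainable variance in the comparison and widens the interval.

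The two sections also do not agree on what is compared. Result variables describes changes, whereas Statistical analysis describes average levels. With up to three follow-up visits for CPD and CO and none singled out, the analysed quantity is open on two counts: final value or change, and which visit. In an open-label trial these are better settled before results are seen.

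Finally, "and its respective post-hoc correction tests" has no clear function beside a t-test of two arms. Post-hoc procedures follow comparisons of three or more groups.

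**Working it through.** **The plan's own figure.** The only sample-size figure is for the primary binary outcome: 3% against 15%, 95% confidence (taken as two-sided alpha 0.05) and 80% power. With the unpooled normal approximation, n = (0.03×0.97 + 0.15×0.85) × (1.960 + 0.842)² / 0.12² = 85.4 per arm, which matches the stated 85. Then 170 × 1.2 = 204. This calculation does not bear on the quantitative outcomes, for which no SD, correlation, target difference or power is given.

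**Assumptions.** r is the correlation between baseline and the follow-up value. It is not in the documents, so a range is shown. The SD is taken as equal at baseline and follow-up.

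**Variance of the arm difference**, relative to a t-test on the final value at one visit (= 1):
- t-test on change: 2(1 − r)
- ANCOVA: 1 − r²
- ANCOVA relative to change: (1 − r²) / [2(1 − r)] = (1 + r)/2

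| r | Change score | ANCOVA | ANCOVA reduction against final value | ANCOVA reduction against change |
|---|---|---|---|---|
| 0.3 | 1.40 | 0.91 | 9% | 35% |
| 0.5 | 1.00 | 0.75 | 25% | 25% |
| 0.6 | 0.80 | 0.64 | 36% | 20% |
| 0.7 | 0.60 | 0.51 | 49% | 15% |

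For any r between 0 and 1, ANCOVA is at least as efficient as either form of the t-test. Below r = 0.5 the change score is worse than the final value; above 0.5 it is better.

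**In terms of power, as an illustration.** If 20% of 204 are lost, 204 × 0.8 = 163 remain, about 82 per arm. Take an assumed true difference of 0.35 SD and two-sided alpha 0.05, and divide the effect by the square root of the variance factor:

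| r | t on final value | t on change | ANCOVA |
|---|---|---|---|
| 0.3 | 61% | 47% | 65% |
| 0.5 | 61% | 61% | 73% |
| 0.6 | 61% | 70% | 80% |
| 0.7 | 61% | 82% | 88% |

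**Repeated visits.** If everyone has complete data, a baseline-adjusted mixed model gives essentially the ANCOVA result at 12 months; the 3- and 6-month values add little. Its benefit comes from patients with partial follow-up, whose earlier CPD and CO values then contribute. Larger gains (variance factor 0.44 at r = 0.3 to 0.31 at r = 0.7, with equal correlation between all visits) arise only for an effect averaged over three visits, which is a different target from the 12-month difference.

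**The case against.** The strongest objection is that the plan may already use baseline. A t-test on changes compares averages between groups, fits the Statistical analysis section and matches the wording of Result variables. This stands: a reader might infer that the plan ignores baseline values, and the documents do not establish that. It does not remove the point, because ANCOVA improves on the change score as well, and the two sections still need reconciling.

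Three other stronger readings also fail:
- That a large part of the information is wasted, or that most follow-up variance is baseline variance. No correlation is given, and at r = 0.5 to 0.7 baseline explains r² = 25% to 49%, which is less than half. The entry floor of 10 CPD says nothing about r, and patients who quit fall to zero whatever their baseline, which could weaken it.
- That separate tests at 3, 6 and 12 months will drop patients who miss a visit. No such tests are stated. The section promises to include all randomised patients, and the handling of missing secondary values is detail that an article may leave to the full plan.
- That motivation is also repeated at 3, 6 and 12 months. The readable text ties those visits to CPD and CO only.

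The phrase on post-hoc corrections could mean a multiplicity correction across outcomes, so it calls for clarification and is not necessarily an error. Lastly, a linear model is imperfect for CPD with a cluster at zero, which is a reason to keep a rank-based analysis alongside it.

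**Conclusion.** The point holds as a modest improvement in efficiency and clarity. The plan names an unadjusted two-group comparison for three outcomes with an available baseline, and leaves open both the quantity and the visit compared. This is a stated method, so it is more than detail left to an analysis plan.

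The gain from baseline adjustment is a 9% to 49% reduction in variance against final values, or 35% to 15% against changes, over r = 0.3 to 0.7. Those figures rest on assumed correlations and equal SDs. They also take CO, like CPD and motivation, to be measured at entry; the schedule figure that would confirm this is not shown.

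Nothing here makes the planned tests invalid. Randomisation protects them, and the primary cessation comparison and its sample size are untouched.

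**What to change.** 1. Analyse each quantitative secondary outcome at 12 months with a linear model (ANCOVA) containing arm and the baseline value of that outcome. Report the adjusted mean difference with its 95% CI. This also settles the question of final value or change, because with baseline in the model the arm effect is the same for both.
2. For CPD and expired CO, optionally use a mixed model over 3, 6 and 12 months with arm, visit, arm-by-visit and baseline, and read off the 12-month difference. Patients with partial follow-up then contribute.
3. Keep a rank-based sensitivity analysis, since CPD may be skewed with a cluster at zero.
4. Align Result variables and Statistical analysis on the quantity and visit compared.
5. Remove the phrase on post-hoc corrections, or, if a multiplicity correction across outcomes is meant, say so and name it.

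The cost is a change of wording and slightly more analysis work. No extra data, visits or patients are needed.
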